## Abstract

**Background:**

While protocol-based psychological treatments have significantly advanced mental health care, real-world accessibility remains a challenge. Primary care, the main provider of mental health services, faces barriers such as limited resources and a diverse patient population with varying needs, making it difficult to rely solely on time-intensive, protocolized treatments. The Primary Care Behavioral Health (PCBH) model promotes brief, flexible interventions that may better accommodate these needs. However, limited research on these interventions raises concerns about potential undertreatment. To align with Universal Health Coverage principles, it is essential to identify which patient groups benefit most from resource-efficient protocol-based versus brief, flexible, and individualized treatments. Our main aim is to evaluate whether a integrating guided self-help into PCBH improves outcomes compared to the core PCBH model, as well as to assess whether patients identified as suitable for protocol-based interventions benefit more from the combined model.

**Methods:**

Patients seeking help for mental or behavioral health problems at PCBH primary care centers will be randomized to one of two arms: core PCBH, where patients receive a contextual assessment and brief interventions tailored to their needs, or an extended PCBH model, where a diagnostic assessment determines whether patients receive brief interventions or guided self-help. The primary outcome is functional impairment, assessed at baseline and followed up at 4, 8, and 12 weeks (primary endpoint), as well as at 1 year. Secondary outcomes include symptom change, cost-effectiveness, and care process factors.

**Discussion:**

The study design allows for comparisons of patient outcomes between the two care models, with a primary focus on evaluating superiority and a secondary focus on non-inferiority, cost-effectiveness, and care process factors. Overall, the project seeks to advance understanding of effective mental health interventions in primary care settings and inform decision-making regarding treatment approaches.

**Trial registration:**

ClinicalTrials.gov: NCT04900064. Registered on May 25th, 2021. Registered with the Swedish Ethical Review Board (2020–04198) on October 12th, 2020. This protocol was submitted for publication on March 18th, 2025, prior to the inclusion of the final participant, and will shortly thereafter, without any changes, be made publicly available as a preprint in an open-access repository.

**Supplementary Information:**

The online version contains supplementary material available at 10.1186/s12913-025-13232-4.

## Background

Over the past decades, the development of empirically supported psychological treatments (ESTs) has been remarkable [1]. Most ESTs are protocol-based cognitive behavioral therapies (CBT) tailored to specific psychiatric disorders [1]. A substantial body of research shows that these can be used to effectively treat common mental health conditions such as depression [2, 3], anxiety disorders [4–8], and insomnia [9]. Despite this progress, the prevalence of mental health issues has not declined at the population level [10], suggesting a gap between advances in research on ESTs and their real-world impact.

Primary care serves as the first point of contact within the healthcare system, ideally providing accessible, person-centered care for a wide range of health concerns. It plays a central role in achieving Universal Health Coverage, which emphasizes equity, access, quality, and financial protection. Given the burden of mental health conditions, it is crucial to understand how psychological interventions can be effectively integrated into primary care to improve public health. However, significant challenges remain in translating the current ESTs into primary care settings. ESTs are often designed for specialist care settings, where treatment intensity and patient selection differ from the realities of primary care. One major issue is limited access: in Sweden, for example, only about 3% of primary care patients have any contact with a mental health professional [11], despite estimates suggesting a point prevalence of depression and anxiety of 17.2% [12]. In fact, ESTs may face even greater scalability challenges – Strosahl and Robinson [13] estimate that a typical primary care clinic would need 12 full-time therapists just to provide in-person ESTs to all patients with depression, underscoring the gap between theoretical efficacy and practical feasibility.

Another key challenge is treatment uptake – although approximately 50% of patients respond to ESTs, this proportion drops to around 20% when accounting for ineligibility, non-attendance, and dropout rates [14]. A possible explanation for these challenges is that solely relying on protocol-driven ESTs may not be well-suited to the primary care context. Primary care patients seek help not only for diagnosable psychiatric disorders but also for broader concerns such as grief, relationship problems, and stress related to work or family issues. Structured assessment tools and diagnostic interviews, while valuable for ensuring accurate diagnosis and guiding appropriate treatment decisions, may inadvertently lead some patients to feel that their concerns are not adequately addressed. This may lead to patients discontinuing treatment prematurely [15].

To address these challenges, population-based healthcare models such as Primary Care Behavioral Health (PCBH) [17] emphasize brief, adaptable interventions that can reach a broader patient population. These approaches often extract core treatment strategies from EST protocols, making them more flexible and responsive to individual patient needs. In many ways, these Brief Interventions (BI) echo the sentiments of process-based therapy, where treatment decisions are based on an assessment of underlying psychological processes rather than diagnoses [16]. However, such adaptations also raise concerns: without systematic assessments followed by well-supported ESTs in their full format, some patients who could benefit from protocol-based treatments may receive suboptimal care.

A key question is how primary care can balance the need for flexible, scalable interventions with the presumed benefits of structured, evidence-based treatment protocols for those who need it. One possibility is to tailor assessment and interventions based on patient needs and circumstances. Patients with subclinical symptoms, challenges primarily related to life stressors, or practical and economic barriers to engaging in time-intensive treatment may benefit more from brief, individualized interventions. In contrast, those with identified psychiatric disorders who can actively participate in structured treatment might achieve better outcomes with protocol-based interventions. Empirical evidence also suggests that some disorders, such as obsessive-compulsive disorder (OCD), require highly specific interventions to achieve meaningful improvement [18], whereas others, such as depression, seem to respond to a wide range of treatment approaches [2]. Identifying which patient groups benefit most from structured ESTs versus flexible, brief interventions could help optimize both access and treatment effectiveness, aligning primary care mental health services with Universal Health Coverage principles.

### Primary Care Behavioral Health (PCBH) and brief interventions (BI)

PCBH emphasizes delivery of brief and acceptable interventions to all patients as part of clinic routine, promoting same-day availability and high productivity [17]. Psychologists or counselors, known in the model as Behavior Health Consultants (BHCs), are core members of the primary care team, working closely with physicians, nurses, and other health professionals in addressing both mental health and behavior-related physical ailments. The model relies on teamwork and task-shifting to ensure cohesiveness for patients and reduce service bottlenecks. While many therapists working within the PCBH framework utilize CBT interventions [18], the delivery model is significantly different. Unlike many ESTs, which follow a structured timeline with a predetermined endpoint (e.g., one session per week for 12 weeks), the PCBH model operates on the presumption that health-promoting behaviors, skills, and habits require ongoing reinforcement – potentially over a lifetime [13]. As such, each individual episode of care is brief, both to ensure they are accessible to the entire population and to allow patients the opportunity to return as needed. Patients typically have 30-minute visits scheduled one at a time. While follow-ups can be booked as needed to assess progress and adjust treatment, the model encourages patients to book additional visits when the need arises rather than pre-planning extended treatments. The assessment procedure, described in detail below, is less focused on diagnostics and more concerned with making an individual conceptualization of how the patient’s context and current coping strategies are connected to their symptoms. An evidence-informed approach is utilized, where modularized core concepts, commonly inspired by the ESTs, are chosen based on an individual analysis [13]. These treatments are commonly referred to as brief interventions (BI).

The practices of PCBH may help expand access to and uptake of psychological interventions [19, 20]. On the other hand, previous studies on the model have limited scientific validity due to consistent methodological weaknesses, where a large problem is the absence of controlled designs. Available pre-post studies suggest that BI in the PCBH framework may improve symptoms, functioning, and well-being across various problem areas, but there is a significant need for higher-quality research [21, 22].

### Guided self-help

Guided self-help (GSH) involves structured, disorder-specific treatments – often grounded in established CBT protocols – delivered through resources such as books or online programs, typically accompanied by limited clinician support [23, 24]. Extensive evaluations of GSH have demonstrated its effectiveness in alleviating symptoms of anxiety and depression, with outcomes comparable to face-to-face CBT [25, 26], while using approximately half the resources [24]. In a primary care setting, research specifically on illness anxiety disorder has shown that self-help books have shown similar effectiveness to internet-based treatments and yielded superior effects compared to waitlist controls [27]. A primary care study of stepped care for common mental disorders found that using self-help books with limited therapist guidance as a first step led to remission in 40% of patients [24].

In summary, GSH appears to be a more resource-efficient alternative to face-to-face CBT while delivering comparable outcomes. However, these treatments remain best suited for patients whose primary or significant concerns align well with existing treatment protocols and who are able and willing to engage in them. In contrast, those whose needs fall outside these parameters may benefit more from BI used in PCBH. This raises an important question: can a resource-efficient version of protocol-driven treatments such as GSH be effectively integrated with high-uptake, individually adaptable interventions within a PCBH-based care model?

### Aim and purpose

The main purpose of the project is to evaluate if adding GSH as a treatment option within the PCBH framework (PCBH + GSH) – offered only to patients deemed suitable following a brief, structured assessment – can enhance treatment outcomes compared to the core PCBH model. Patient outcomes in the research questions below include everyday functioning (primary outcome) as well as disorder-specific symptoms. The research questions are as follows:

Primary question: When comparing patient outcomes at the care model level after 12 weeks, is PCBH + GSH more effective than the core PCBH model? If not, can non-inferiority of core PCBH be established?Among the subgroup of patients deemed suitable for structured interventions in both groups, do those receiving GSH in PCBH + GSH achieve better outcomes than those receiving BI in core PCBH? Additionally, is this effect more pronounced in patients with conditions expected to require specific treatment components, such as exposure therapy for anxiety disorders, compared to those with conditions like depression and stress, where the benefits of specific treatment components are less clearly established? If not, can non-inferiority of BI be established for these subgroups?Does adding GSH to PCBH increase treatment duration or costs of care delivery? Which model is more cost-effective, considering patient benefits in relation to healthcare and societal costs?Do the care models and treatments differ in patient satisfaction, adverse events, treatment content, and which behavioral changes patients make during and after treatment?Will the protocol-based intervention of GSH decrease variation in treatment outcome compared to BI, especially when comparing patients deemed suitable for structured interventions?In BI, do patients whose therapists use techniques aligned with evidence-based strategies for the patient’s specific symptoms (e.g., exposure for anxiety) achieve better outcomes? How do outcomes differ for various subgroups of patients receiving BI under different conditions, and how do these compare to the group receiving GSH? In GSH, how do therapists’ adherence to treatment protocols impact outcomes? More broadly, how does the specific treatment content, independent of which type of intervention it is provided in, influence patient outcomes?

Additionally, we want to explore if the PCBH + GSH model is feasible for large-scale implementation in healthcare.

7.What proportion of patients are considered suitable for GSH following an extended diagnostic assessment? How does this proportion vary across different primary care centers and over time within a center? What factors contribute to this variation?8.How do patient-related outcomes differ between centers and therapists, and what factors contribute to these variations? Do these differ depending on which treatment is given?9.To what extent are GSH treatments delivered with fidelity to GSH principles within the PCBH framework, particularly in areas where PCBH and GSH principles conflict (i.e. booking practices, prioritizing treatment fidelity versus maximizing access)? Are BI treatments delivered in accordance with PCBH principles and the evidence-base? How does fidelity vary across therapists and primary care centers, and what factors contribute to this variation?

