#### Retrospective algorithm for assessing indication for structured treatment

To address research question (2) – which examines whether patients who would have been suitable for GSH but did not receive it face a risk of undertreatment – we have developed an assessment model to retrospectively evaluate patients’ indications for structured treatment related to mood disorders, anxiety, stress-related conditions, or insomnia among those randomized to the core PCBH model. The assessment model is designed to mirror the clinicians’ extended, diagnostic assessment as closely as possible, with the crucial distinction that categorization is based solely on self- and clinician-reported data, and patient treatment preferences are unknown since they are never offered the possibility to receive GSH. Patients in the core PCBH arm who are retrospectively assessed as not indicated for structured treatment are assigned to the CORE-N-BI group, while those who meet the criteria are placed in the CORE-I-BI group. The same retrospective assessment will be conducted for patients in the extended PCBH arm to allow for comparisons between the retrospective and real-life assessments; however, this will not impact their group assignment.

The retrospective assessment consists of four steps:

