### Data analysis plan

Due to the pragmatic nature of the study, where randomization occurs early – after patients have been identified and invited to participate, but before they are formally included in the trial – there is an increased risk of randomized participants during assessment or treatment being deemed unsuitable for both GSH and BI due to a need for specialized or primarily medical treatment. These participants will be excluded from most analyses but are expected to be randomly distributed between study arms. Another consequence of the pragmatic design is that patients may complete the pre-treatment measures up to a week after their initial visit to manage the usually very brief waiting time in PCBH. This could particularly impact within-group BI effects, as treatment begins during the first visit. To address this, a sensitivity analysis excluding late responses will be conducted, along with an analysis of missing data to evaluate its potential impact.

Several comparisons will be made to address the research questions. For research questions (1) and (3), we will conduct between-group comparisons on primary and secondary measures at the care model level, specifically comparing all participants in PCBH group with those in the PCBH + GSH group. To address research question (2), we will compare the subgroup of patients who received GSH (the EXT-I-GSH group) within the PCBH + GSH model with those who were retrospectively assessed as indicated for structured treatment but were randomized to the core PCBH arm and therefore did not receive GSH (the CORE-I-BI group). For the subgroup analysis examining whether GSH has a greater impact on conditions where the protocol is expected to have more specific effects (insomnia, panic disorder, social phobia, health anxiety disorder, and OCD) compared to conditions the effects are expected to be more general and non-specific (depression, GAD, and stress), analyses will evaluate whether patients in the former group show larger differences between GSH and BI than patients in the latter group. Research question (4) will be analyzed at both the care model and treatment type levels, as factors such as patient satisfaction, treatment content, patient behavior, and adverse events may be influenced by both the assessment and treatment strategies.

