For research questions (5) and (6), the analysis groups will be defined based on treatment rather than the model of care. It is therefore essential to clarify how comparison groups are categorized, as they do not align fully with the randomized groups. There is only one subgroup of patients that receive GSH – the patients in the PCBH + GSH arm assessed by the clinician as suitable for GSH (the EXT-I-GSH group). In contrast, patients receiving BI can be divided in several groups, all presented in Table 3. Analyses will be conducted on various combinations of patients receiving BI to account for potential differences among these groups. For example, CORE-N-BI and EXT-N-BI may present with more complex symptoms or social challenges compared to CORE-I-BI – or alternatively, they may have less complex, transient life stressors. Additionally, the diagnostic assessment in the PCBH + GSH model may influence the effectiveness of BI in either direction, necessitating comparisons between patients who received BI in the core model and those in the extended model.

**Table 3 Tab3:** Treatment-level analysis groups

	Core PCBH arm		PCBH + GSH arm	
	CORE-I-BI	CORE-N-BI	EXT-I-GSH	EXT–N-BI
**All patients receiving GSH**			X	
**All patients receiving BI**	X	X		X
**Receiving BI despite an indication for structured treatment**	X			
**Receiving BI in accordance with the indicated treatment**		X		X
**Receiving BI following an extended assessment confirming BI as appropriate**				X
**Receiving BI after the contextual interview**	X	X		

Notes. CORE-I-BI = Patients receiving brief interventions (BI) within the core PCBH model who were retrospectively assessed as suitable for structured treatment

CORE-N-BI = Patients receiving brief interventions (BI) within the core PCBH model who were retrospectively assessed as not suitable for structured treatment

EXT-I-GSH = Patients receiving guided self-help (GSH) after undergoing an extended diagnostic assessment within the PCBH + GSH model, where they were deemed suitable for structured treatment

EXT-N-BI = Patients receiving brief interventions (BI) after an extended diagnostic assessment within the PCBH + GSH model, where they were not deemed suitable for structured treatment

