## Discussion

In this study protocol, we present a comprehensive framework for evaluating the effectiveness of the PCBH + GSH model compared to the core PCHB model. Additionally, we aim to increase knowledge of which patient groups benefit most from which type of intervention as well as test an assessment model that could be integrated into standard healthcare practice. Our aim is to generally expand the evidence base for PCBH and specifically explore whether GSH can complement the treatment options. We also seek to investigate the cost-effectiveness associated with the PCBH + GSH model compared to core PCBH and evaluate several aspects related to care processes and implementation. These findings will offer valuable insights for optimizing healthcare resource allocation and mental health service delivery in primary care settings.

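### Research question 2 compares arms only within suitable patients, so it cannot show that suitable patients benefit more than others, and it estimates assessment plus GSH rather than GSH alone

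*Protocol article*

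**What the plan says.** The abstract (Background) gives as part of the main aim "to assess whether patients identified as suitable for protocol-based interventions benefit more from the combined model". The Discussion adds: "we aim to increase knowledge of which patient groups benefit most from which type of intervention".

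Under Aim and purpose, research question 2 is restricted to patients deemed suitable for structured interventions and asks "do those receiving GSH in PCBH + GSH achieve better outcomes than those receiving BI in core PCBH". The Data analysis plan assigns one contrast to it: EXT-I-GSH (extended arm, received GSH) against CORE-I-BI (core arm, retrospectively judged indicated, received BI). The two not-indicated cells of Table 1 are not used.

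Two related analyses are planned:

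- **By condition type.** For conditions with expected specific effects against those with non-specific effects, "analyses will evaluate whether patients in the former group show larger differences between GSH and BI than patients in the latter group".
- **By assessment.** The plan recognises that "the diagnostic assessment in the PCBH + GSH model may influence the effectiveness of BI in either direction", and the same sentence goes on to call for comparing BI recipients in the core model with those in the extended model. This stands with research questions 5 and 6.

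On the rating of indication, the section on the retrospective algorithm says: "The same retrospective assessment will be conducted for patients in the extended PCBH arm to allow for comparisons between the retrospective and real-life assessments".

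**The concern.** Whether suitable patients benefit more than not-suitable patients is a question of effect modification. It needs the arm difference in both strata and the difference between the two. The plan states the first stratum's arm difference and no more. A significant result in suitable patients is compatible with an equal, or even larger, effect in the rest.

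The contrast inside the stratum is also not one of treatments. The Design section says that randomisation is between models of care. EXT-I-GSH patients had a diagnostic assessment over two visits, kept separate from intervention, and then GSH. CORE-I-BI patients had a contextual interview, itself regarded as therapeutic, with an intervention at the first visit. Reporting the difference as GSH against BI credits one component with the effect of the package.

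At stake is how a positive result is read: as evidence that suitability identifies who gains from the extended model, or that GSH is the active part. The planned contrast supports neither by itself.

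**Working it through.** **Inputs.** From Power analysis: d = 0.20, power 80%, alpha 0.05 (two-sided, inferred), 20% missing at FU12, N = 983; non-inferiority N = 775. From Design: 1:1 allocation. The suitable share p is not given, so p = 0.3 to 0.7 is an assumption. Effects are in SD units. The calculation uses the normal approximation, takes p as equal in both arms and allocation as 1:1 within strata, and ignores clustering.

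**The plan's own figures.**
- Superiority: n per arm = 2 × (1.960 + 0.842)² / 0.20² = 392.4, so 393; total 786; 786 / 0.80 = 982.5, so 983. Reproduced.
- Non-inferiority (one-sided 0.05): n per arm = 2 × (1.645 + 0.842)² / 0.20² = 309.1, so 310; total 620; 620 / 0.80 = 775. Reproduced.

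There is no sample size error. The figures below use 786 analysed patients.

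**Formulas.**
- SE of the arm difference in suitable patients: √(4 / (786p)). At p = 0.5: √(4/393) = 0.101.
- SE of the interaction: √(4 / (786p) + 4 / (786(1 − p))). At p = 0.5: √(4/393 + 4/393) = 0.143.
- Power for an effect δ: Φ(δ/SE − 1.960).
- Interaction detectable with 80% power: 2.802 × SE.

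**Results.**

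| p | SE, suitable | P(RQ2 significant) if d = 0.20 in everyone | SE, interaction | Detectable interaction | Power, interaction of 0.20 | Interaction power if the whole effect is in suitable patients (d = 0.20/p) |
|---|---|---|---|---|---|---|
| 0.3 | 0.130 | 0.34 | 0.156 | 0.44 | 0.25 | 0.99 (d = 0.67) |
| 0.4 | 0.113 | 0.43 | 0.146 | 0.41 | 0.28 | 0.93 (d = 0.50) |
| 0.5 | 0.101 | 0.51 | 0.143 | 0.40 | 0.29 | 0.80 (d = 0.40) |
| 0.6 | 0.092 | 0.58 | 0.146 | 0.41 | 0.28 | 0.63 (d = 0.33) |
| 0.7 | 0.085 | 0.65 | 0.156 | 0.44 | 0.25 | 0.45 (d = 0.29) |

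The third column is the main result. With the same benefit in everyone, there is nothing to find about who benefits more, yet research question 2 is significant in the expected direction in 34 to 65% of trials. The same probabilities apply if the extended assessment alone gave d = 0.20 and GSH added nothing. An interaction test would reject in 5% under a uniform effect.

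**Price of the interaction.** The SE for research question 1 is √(4/786) = 0.071, so the interaction SE is 2.0 to 2.2 times as large. For an interaction of d = 0.20, 80% power would need 3140 to 3738 analysed patients, or 3925 to 4672 recruited with 20% missing.

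**The case against.** - **Question and analysis agree.** Research question 2 is explicitly confined to suitable patients, and the abstract's phrase can mean that they do better under the combined model than under the core model. That is a fair reading, and the planned contrast addresses it. The Discussion's aim about which groups benefit most does not depend on that reading.
- **Effect modification is planned.** It is, by condition type. That covers part of the Discussion's aim but stays within suitable patients, so it says nothing about suitable against not-suitable.
- **The assessment effect is recognised.** A reader might infer that the plan ignores it. It does not: core-versus-extended BI comparisons are planned. They help only in part. They are not linked to research question 2. Table 3 pools CORE-I-BI with CORE-N-BI in its row for BI after the contextual interview, while BI after the extended assessment is EXT-N-BI alone. Indication is rated retrospectively in one arm and by the clinician in the other, and patients who decline GSH receive BI.
- **An interaction would not isolate GSH.** This stands. A reader might take the arm difference in not-indicated patients as the effect of the assessment and subtract it. The section on the extended assessment lets clinicians skip the assessment when a patient is clearly unsuitable, so that stratum may receive less of it. The documents also give no agreement between retrospective and clinician ratings.
- **Low power, secondary question.** Also true. The interaction reaches 80% power at a 50% share only if the whole effect lies in suitable patients; at a 60% share the figure is 63%. The plan performs no power analysis for research question 2. This makes the interaction exploratory; it does not make the within-stratum result a substitute for it.

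**Conclusion.** The point holds in limited form. As planned, research question 2 estimates the effect of the extended pathway (assessment plus GSH) against the core pathway (contextual interview plus BI) in suitable patients. It cannot show that suitable patients benefit more than not-suitable ones, and it is not a contrast of GSH with BI alone. The planned condition-type and BI comparisons narrow this gap but do not close it.

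The size depends on a suitable share that the documents do not give. Over 30 to 70%, a uniform d = 0.20 would make the comparison significant with probability 0.34 to 0.65. The uniform effect is an illustration; nothing in the documents says that the assessment alone would produce it.

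Two stronger conclusions are not supported: that the trial leaves the question of who benefits most wholly unaddressed, and that a positive result would lead to a recommendation to sort patients by suitability. The documents state no such recommendation.

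**What to change.** 1. As a secondary, exploratory analysis on all included patients as randomised, add retrospective indication and its interaction with arm to the research question 1 model. Use the rating from the same retrospective algorithm in both arms, not the clinician's decision in the extended arm.
2. Report the FU12 arm difference in indicated patients, in not-indicated patients, and the difference between the two with its confidence interval. Base any statement that suitable patients benefit more on that last figure.
3. Describe the research question 2 result as the effect of the extended pathway in suitable patients. Do not present the interaction as separating GSH from the assessment.

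The cost is small in effort: the ratings are already planned in both arms, so it takes one factor with its interaction in a model and a few table rows. The real cost is precision. With an interaction SE of 0.143 to 0.156, only differences of d = 0.40 to 0.44 are detectable with 80% power, and power for d = 0.20 is 25 to 29%. The report should say that a null interaction does not show equal benefit.
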